**Methods:**

TRIC‐I‐HF‐DZHK24 (NCT04634266) is an investigator‐initiated, prospective, randomized, open‐label, multicentre strategy trial. Approximately 360 patients with severe TR and manifest right‐sided HF will be enrolled. In contrast to previous trials, subjects with increased risk for HFH will be selected as facilitated by specific inclusion criteria: HFH in the previous year, or presence of cardio‐renal syndrome, or evidence for cardio‐hepatic syndrome. Subjects will be randomized 2:1 to TTVI and optimal medical therapy (OMT) or continuation of OMT alone. All CE‐marked transcatheter repair devices including tricuspid transcatheter edge‐to‐edge repair (T‐TEER) or transcatheter tricuspid annuloplasty can be used for TTVI. The participating 29 study sites are highly experienced and treated a mean of 176 patients in 4.5 years with T‐TEER before study activation. The primary outcome will be assessed at 1 year. First, a composite of all‐cause mortality, HFH, and QoL improvement will be tested hierarchically. If positive, the combination of hard clinical endpoints including all‐cause mortality and HFH will be tested. Patients will be followed for a total of 3 years. The safety outcome comprises complications of TTVI, life‐threatening bleeding and death.

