## Introduction

Tricuspid regurgitation (TR) is a highly prevalent disease independently associated with increased morbidity and mortality.^1^, ^2^ Medical treatment options are limited, and surgical results for isolated TR are discouraging in heart failure (HF) patients carrying increased operative risk.^3^, ^4^ While patients with severe TR and HF have been left without treatment options for many years, several transcatheter tricuspid valve interventions (TTVI) have been introduced in recent years. Tricuspid transcatheter edge‐to‐edge repair (T‐TEER) is the most frequently applied technique and received CE‐mark in the year 2020. Post‐market registries demonstrated high technical success rates and a very good safety profile of the available devices.^5^, ^6^ Propensity‐score matched prospective observational studies suggested a reduction of HF hospitalization (HFH) after TTVI in patients with significant right‐sided HF.^7^ Recent randomized controlled trials confirmed the safety of the technique and demonstrated significant improvement of quality of life (QoL) after T‐TEER, while HFH and mortality were unaffected.^8^, ^9^ However, both the TRILUMINATE Pivotal and Tri.Fr trials enrolled symptomatic patients but without additional selection criteria for right‐sided HF. Accordingly, the associated event rates for mortality and HFH within the trials were comparably low (1‐year mortality rate: 8.6% in TRILUMINATE Pivotal, and 3.4% in Tri.Fr).^8^, ^9^ Hence, the effect of TTVI in patients with manifest HF and underlying TR at advanced stages of the disease process remains unsolved. Therefore, the TRIC‐I‐HF‐DZHK24 (TRICuspid Intervention in Heart Failure) trial has been designed to assess the concept that TTVI will translate into a reduced morbidity and mortality in patients with severe TR and evidence for manifest right‐sided HF. TRIC‐I‐HF‐DZHK24 is an investigator‐initiated clinical strategy study and investigators may choose any suitable CE‐marked percutaneous system ‘on‐label’ for tricuspid valve repair. Transcatheter tricuspid repair devices for TTVI include T‐TEER and direct transcatheter tricuspid annuloplasty. Compared to the above mentioned previous clinical trials, the TRIC‐I‐HF‐DZHK24 study sites are considerably more experienced, and many sites accumulated T‐TEER experience before study initiation and even before devices received CE mark in 2020 by ‘off‐label’ MitraClip implantation. Patients will be randomly assigned in a 2:1 fashion to TTVI in addition to optimal medical therapy (OMT) (interventional group) or OMT alone (control group).

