#### Secondary endpoints

Secondary endpoints include all‐cause mortality, HFH (including frequency and length), change in QoL as assessed by KCCQ, re‐intervention for recurrent TR, change in NYHA functional class from baseline, change of 6‐min walking distance from baseline, change in echocardiographic parameters, change in peripheral oedema and subject weight, change of diuretic and HF medication from baseline, and change in laboratory markers for cardiac, renal and hepatic function. Sub‐group analyses are planned for different repair strategies. All endpoints are listed in *Table* *3*.

**Table 3 ejhf3795-tbl-0003:** Primary and secondary endpoints of the trial

**Hierarchical primary endpoint analysis** First primary endpoint: composite of all‐cause mortality, number of HFH, and lack of QoL improvement at 12 months. Second primary endpoint (tested only, if first primary endpoint is statistically significant): time to all‐cause mortality or HFH, whichever occurs first at 12 months.
**Secondary endpoints** All‐cause mortality Frequency and length of HFH Change in quality of life as assessed by KCCQ Re‐intervention rates for recurrent tricuspid regurgitation Change in NYHA class from baseline Change in 6‐min walk test distance from baseline Change in echocardiographic parameters (among others: TR grade, RV dimension and function, LV dimension and function, estimation of sPAP) Development of tricuspid stenosis (mean inflow gradient >5 mmHg) Change in peripheral oedema and subject weight Change in diuretic drugs and heart failure medications from baseline Change in laboratory markers for cardiac, renal and hepatic function
**Safety endpoint** Major adverse events related to the intervention during the first month, including mortality, life threatening bleeding (BARC classification type 3 and 5), major vascular or cardiac structural complications requiring intervention, or mechanical circulatory support.

BARC, Bleeding Academic Research Consortium; HFH, heart failure hospitalization; KCCQ, Kansas City Cardiomyopathy Questionnaire; LV, left ventricular; NYHA, New York Heart Association; QoL, quality of life; RV, right ventricular; sPAP, systolic pulmonary arterial pressure; TR, tricuspid regurgitation.

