### Statistical analysis

A sample size of 224 patients in the interventional arm and 112 patients in the control arm (total of 336 patients) are required to achieve 85% power assuming a win ratio of 1.818 and a significance level of 5% for a two‐sided test. This assumes the proportion of wins is 0.4, the proportion of losses is 0.22, and the proportion of ties is 0.38. Assuming a drop‐out rate of 10%, a total of 360 patients must be randomized, 240 patients in the interventional arm, and 120 patients in the control arm. All analyses will be performed on the full analysis set according to the intention‐to‐treat principle. Further, sensitivity analyses according to the per‐protocol set will also be performed.

The two primary endpoints will be analysed in a hierarchical testing procedure. The second primary endpoint will only be analysed, if the first primary endpoint delivers statistically significant results. The first primary endpoint will be analysed using the Finkelstein and Schoenfeld method, which calculates a win ratio based on pairwise comparisons between all possible patient pairs from the two treatment groups. In each pair, a ‘winner’ is determined by hierarchical comparison: first, based on time to all‐cause mortality; if both patients are alive or die at the same time, then based on the number of HFH; and if still tied, based on change in KCCQ score at 12 months. The win ratio is defined as the total number of wins in the treatment group divided by the total number of losses. The statistical significance of the win ratio will be evaluated at a two‐sided alpha level of 5%. The second primary endpoint, event‐free survival (composite of all‐cause mortality and HFH), will be evaluated using a two‐sided log‐rank test stratified by TR grading at a significance level of 5%, provided that the first primary endpoint shows a statistically significant result as per the hierarchical testing procedure. Kaplan–Meier analyses will be conducted for both treatment groups, and event‐free probabilities will be reported at 1, 2, and 3 years of follow‐up.

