Secondary endpoints will be compared between the study arms using explorative statistics. The explorative significance level will be set to 5% and no adjustment will be made for multiple testing. Baseline and follow‐up demographic data will be described using standard descriptive statistics including frequency distributions, means and standard deviations, and medians and interquartile ranges. Cumulative incidence for all‐cause mortality and HFH will be calculated and presented as Kaplan–Meier time‐to‐event curves with comparison of the control and interventional arm.

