## Discussion

The TRIC‐I‐HF‐DZHK24 trial is a multicentre, prospective, controlled, randomized, open‐label clinical study assessing the impact of TTVI on top of OMT in patients with HF due to underlying severe TR. T‐TEER is the best available, most abundantly used, and safest TTVI technique. Previous randomized controlled trials, namely the TRILUMINATE Pivotal and Tri.Fr trials, demonstrated a superiority of T‐TEER regarding QoL improvement, however, these trials could not identify an effect on all‐cause mortality and HFH.^8^, ^9^, ^13^ By specific inclusion criteria, the TRIC‐I‐HF‐DZHK24 trial will select for more advanced HF patients that are deemed at higher risk for HFH and will possibly benefit more from TTVI, than patients enrolled in TRILUMINATE Pivotal and Tri.Fr. The first primary endpoint is a composite of all‐cause mortality, HFH and patient‐centred QoL improvement. If this first primary endpoint is positive, a second primary endpoint, solely composed of hard clinical endpoints including all‐cause mortality and HFH at 1 year, will be tested hierarchically. Cross‐over from the control arm to the interventional arm is possible as important tool to enhance patient enrolment in a setting of commercially available TTVI devices, however, cross‐over procedures are only allowed by study protocol in the event of significant HFH with the necessity of intravenous diuretic therapy and after a blanking period of 1 month post‐randomization. Thus, the trial has the potential to bring definite evidence of TTVI on hard clinical endpoints in a high‐risk patient population.

Previous randomized controlled trials in the field of TTVI tested the impact of a specific device. In the TRILUMINATE Pivotal and Tri.Fr trials, only TriClip devices were implanted. In contrast, TRIC‐I‐HF‐DZHK24 is a strategic trial evaluating the impact of tricuspid valve repair by the utilization of commercially certified devices with CE mark. Another advantage of TRIC‐I‐HF‐DZHK24 in comparison to previous trials is the distinct TTVI experience of participating study sites, possibly resulting in improved procedural results with positive effect on study outcomes. Mean site experience in T‐TEER before local activation of the trial was very high: 176 ± 163 T‐TEER procedures, 54 ± 26 months of T‐TEER experience. Many sites collected experience in T‐TEER by off‐label implantation of MitraClip, before TriClip and PASCAL systems received CE mark in 2020.

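### The cumulative incidence of heart failure hospitalization (HFH) is to be shown by Kaplan–Meier, which censors deaths and overstates the HFH percentages; a low-severity correction to an exploratory display

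*Protocol article*

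**What the plan says.** In the paragraph on secondary endpoints, the Statistical analysis section of the protocol article states: "Cumulative incidence for all‐cause mortality and HFH will be calculated and presented as Kaplan–Meier time‐to‐event curves", with the two arms compared. It thus names both the quantity (cumulative incidence) and the method (Kaplan–Meier). No competing-risk estimator is named anywhere in the article, and death is not identified as a competing event for HFH.

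The Secondary endpoints section lists death and HFH as separate items: "Secondary endpoints include all‐cause mortality, HFH (including frequency and length"; Table 3 does the same. The composite of death or HFH is dealt with earlier in Statistical analysis, with a stratified log-rank test and this statement: "Kaplan–Meier analyses will be conducted for both treatment groups, and event‐free probabilities will be reported at 1, 2, and 3 years of follow‐up".

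On follow-up, the abstract says: "Patients will be followed for a total of 3 years". On risk, the Introduction gives figures from two earlier trials only ("1‐year mortality rate: 8.6% in TRILUMINATE Pivotal, and 3.4% in Tri.Fr"), and the Discussion says that this trial "will select for more advanced HF patients that are deemed at higher risk for HFH".

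**The concern.** Death prevents any later HFH. A Kaplan–Meier curve for HFH alone has to treat a patient who dies without HFH as censored, that is, as someone who could still have been admitted later. One minus that curve is the HFH risk in a hypothetical population without deaths. It is not the proportion of patients who are actually hospitalized, which is what cumulative incidence means. Kaplan–Meier is correct for all-cause mortality and for death-or-HFH, because neither has a competing event.

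At stake are the HFH percentages reported for each arm and the difference between them. The Discussion calls HFH the most important component of the primary endpoint, so readers will look at these curves. Because the article names the method, this is not a detail left to an analysis plan.

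**Working it through.** **Reading the sentence.** If it meant the composite, it would repeat what the same section has already planned for event-free survival. It stands in the secondary-endpoint paragraph, and the two outcomes are listed separately in the Secondary endpoints section and in Table 3. HFH alone is therefore the natural reading, though not the only possible one.

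**The plan's own figures.** No stated figure depends on this estimator. The sample size uses win, loss and tie proportions and no event rates: N = (1.960 + 1.036)² × σ² / (ln 1.818)², with σ² = 4(1 + 0.38) / [3 × (2/3) × (1/3) × (1 − 0.38)] = 13.36. This gives 335.6, so the stated 336 reproduces. It supplies no HFH or mortality rate.

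**Formulas.** Let h be the yearly hazard of first HFH and d the yearly hazard of death *without prior HFH*, both constant.

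- One minus Kaplan–Meier: 1 − exp(−h·t)
- Cumulative incidence (what Aalen–Johansen estimates): h/(h + d) × [1 − exp(−(h + d)·t)]

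**Inputs, all assumed for this trial.**

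- Case A: 1-year HFH of 25% on the Kaplan–Meier scale, so h = −ln(0.75) = 0.2877; d = −ln(1 − 0.086) = 0.0899. The 8.6% is the higher of the two earlier 1-year mortality rates in the Introduction, used here as if every death came before any HFH.
- Case B: h = 0.40, d = 0.15.
- Case C: as B, but half of all deaths follow an HFH, so d = 0.075.

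| Case | Year | 1 − KM | Cumulative incidence | Excess (points) |
|---|---|---|---|---|
| A | 1 | 25.0% | 24.0% | 1.0 |
| A | 3 | 57.8% | 51.6% | 6.2 |
| B | 1 | 33.0% | 30.8% | 2.2 |
| B | 3 | 69.9% | 58.8% | 11.1 |
| C | 3 | 69.9% | 64.0% | 5.9 |

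Worked for B at 3 years: 1 − exp(−1.2) = 0.699; (0.40/0.55) × [1 − exp(−1.65)] = 0.7273 × 0.8080 = 0.588.

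**Range.** For 1-year HFH from 15% to 40% and death without prior HFH from 3.4% to 25% per year, the excess is 0.2 to 4.8 points at 1 year and 1.8 to 20.3 points at 3 years.

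**Between-arm difference at 3 years, with assumed hazards (h/d).**

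- Control 0.40/0.15, intervention 0.30/0.10. Kaplan–Meier: 69.88 − 59.34 = 10.5 points. Cumulative incidence: 58.76 − 52.41 = 6.35 points.
- Control 0.40/0.15, intervention 0.40/0.10. Kaplan–Meier: no difference. Cumulative incidence: 62.15 − 58.76 = 3.4 points *higher* with the intervention, because more patients survive to be admitted.

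**The case against.** **The wording is ambiguous.** The article elsewhere joins all-cause mortality and HFH in the same way when it means the composite, for which Kaplan–Meier is right. This stands as a reason to ask for clarification. It does not displace the more natural reading.

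**A high-mortality population is not documented.** A reader might infer one from the selection of advanced patients. The documents do not support stating it as fact: the extra criteria select for HFH risk, patients with a life expectancy below 12 months are excluded, and the only mortality rates given come from earlier trials. This stands.

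**The 3-year horizon is assumed.** The sentence gives no time horizon. The 1-, 2- and 3-year estimates are specified with the composite. Three-year HFH curves are plausible given the length of follow-up, but they are not stated. This stands, and the larger figures depend on it.

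**Only deaths without a prior HFH compete.** Putting all-cause mortality into d overstates the bias, because deaths after a first HFH do not affect the curve. Case C shows the 11 points falling to about 6. This stands.

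**The treatment comparison may be sound.** A reader might infer that the error inflates the treatment benefit on HFH. That is true only of the difference in incidence when mortality is lower in the intervention arm. A log-rank or Cox comparison with deaths censored compares cause-specific hazards and remains valid. In the second two-arm example it correctly shows equal HFH hazards.

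**It is exploratory.** Secondary endpoints carry no confirmatory claim, and mortality is reported alongside. This stands and limits the severity.

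**Conclusion.** The point holds as a low-severity correction. On the natural reading, the article pairs cumulative incidence of HFH with an estimator that does not estimate it. The direction of the bias is certain whenever any patient dies without a prior HFH. Its size is not known, because the documents give no event rates for this trial. Under constant assumed hazards the excess is about 1 to 2 points at 1 year. If the curves extend to 3 years, it is about 6 points in case A and about 11 in case B. The between-arm difference in incidence is also distorted if mortality differs by arm.

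A reader might conclude that the trial's main HFH result is compromised. The documents do not support that: the win ratio compares death before HFH, the second primary endpoint counts death as an event, and cause-specific hazard comparisons are valid. What is wrong is the absolute HFH percentages, and their difference, in an exploratory secondary display.

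**What to change.** - Estimate the cumulative incidence of HFH by arm with the Aalen–Johansen estimator, with death as competing event, and state the time horizon.
- Compare arms with the cause-specific hazard ratio for HFH, shown beside the mortality result. Gray's test is not an interchangeable alternative: it compares cumulative incidence functions, and the second two-arm example shows that the two contrasts can disagree.
- Keep Kaplan–Meier for all-cause mortality and for death-or-HFH.
- If the sentence was meant for the composite, say so; Kaplan–Meier then stands.

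The cost is a sentence of wording and a standard procedure. The dates of death and HFH are already needed for the primary endpoints, so no new data are required. The downside is that the reported HFH percentages will be lower than on the Kaplan–Meier scale. They will also depend on mortality, which is why they should be read next to the mortality result.

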## Discussion

The TRIC‐I‐HF‐DZHK24 trial is a multicentre, prospective, controlled, randomized, open‐label clinical study assessing the impact of TTVI on top of OMT in patients with HF due to underlying severe TR. T‐TEER is the best available, most abundantly used, and safest TTVI technique. Previous randomized controlled trials, namely the TRILUMINATE Pivotal and Tri.Fr trials, demonstrated a superiority of T‐TEER regarding QoL improvement, however, these trials could not identify an effect on all‐cause mortality and HFH.^8^, ^9^, ^13^ By specific inclusion criteria, the TRIC‐I‐HF‐DZHK24 trial will select for more advanced HF patients that are deemed at higher risk for HFH and will possibly benefit more from TTVI, than patients enrolled in TRILUMINATE Pivotal and Tri.Fr. The first primary endpoint is a composite of all‐cause mortality, HFH and patient‐centred QoL improvement. If this first primary endpoint is positive, a second primary endpoint, solely composed of hard clinical endpoints including all‐cause mortality and HFH at 1 year, will be tested hierarchically. Cross‐over from the control arm to the interventional arm is possible as important tool to enhance patient enrolment in a setting of commercially available TTVI devices, however, cross‐over procedures are only allowed by study protocol in the event of significant HFH with the necessity of intravenous diuretic therapy and after a blanking period of 1 month post‐randomization. Thus, the trial has the potential to bring definite evidence of TTVI on hard clinical endpoints in a high‐risk patient population.

Previous randomized controlled trials in the field of TTVI tested the impact of a specific device. In the TRILUMINATE Pivotal and Tri.Fr trials, only TriClip devices were implanted. In contrast, TRIC‐I‐HF‐DZHK24 is a strategic trial evaluating the impact of tricuspid valve repair by the utilization of commercially certified devices with CE mark. Another advantage of TRIC‐I‐HF‐DZHK24 in comparison to previous trials is the distinct TTVI experience of participating study sites, possibly resulting in improved procedural results with positive effect on study outcomes. Mean site experience in T‐TEER before local activation of the trial was very high: 176 ± 163 T‐TEER procedures, 54 ± 26 months of T‐TEER experience. Many sites collected experience in T‐TEER by off‐label implantation of MitraClip, before TriClip and PASCAL systems received CE mark in 2020.

Several methodological strengths in the design of the trial will improve the validity of the study results. First, echocardiographic data are independently reviewed by a central echo core lab to improve data quality of TTE and TOE image data including TR severity as well as right heart and left heart function. Second, a clinical event committee will adjudicate the correctness of HFH that is the most important component of the primary endpoint. Third, invasive haemodynamic assessment by right heart catheterization will be available in all patients of the trial since results of right heart catheterization are part of the in‐ and exclusion criteria. This facilitates comprehensive haemodynamic characterization of all patients enrolled into the trial.

### Limitations

The study has several limitations that warrant discussion. First, the study design will induce a selection bias with recruitment of patients at high‐volume sites. However, the experience of heart valve centres has been identified as significant contributor for clinical success and will improve the overall quality of the study.^6^ Second, the absence of a central screening committee might cause certain heterogeneity between study sites, however, eligibility for trial participation is defined by in‐ and exclusion criteria and is regularly monitored. Third, local investigators select eligible patients by identification of severe TR and clinical assessment of right‐sided HF. Patients with primarily left‐sided HF and neurohormonal activation can also develop fluid retention, peripheral oedema, and significant TR, and thus, might satisfy inclusion criteria for trial enrolment. Fourth, TRIC‐I‐HF‐DZHK24 selects patients with advanced right‐sided HF and increased risk for HFH due to specific selection criteria. The selection criteria ‘cardio‐renal syndrome’ might be influenced by concomitant diseases such as hypertensive or diabetic nephropathy. Fifth, the study requires multiple in‐hospital follow‐up visits of elderly patients with often reduced physical capacities. The risk of patients lost to follow‐up and incomplete data will be mitigated by multiple reminder strategies. Sixth, although mortality and HFH will be tested as hard clinical endpoints in TRIC‐I‐HF‐DZHK24, patient‐centred QoL outcomes are included in the first primary composite outcome by win‐ratio analysis of the KCCQ score. Finally, the lack of a sham procedure in the control group carries the risk of a placebo effect in the interventional arm with impact on patient‐centred QoL outcomes.

